### Outcome measures

#### Primary outcome measure

The primary outcome measure is pneumonia within 30 days after trauma. In order to define pneumonia, the flowchart of the Centers of Disease Control and Prevention, based on imaging and clinical and laboratory criteria, will be followed (Fig. 1) [42]. Temperature (*T*) will be measured daily during admission. If *T* > 38.0 °C intra-auricular (or *T* > 39 °C rectal), bladder, central, or a sputum culture will be done. Also, the wound will be checked (if applicable) and a radiograph of the thorax will be made. If patients are suffering from fever at home, they will be advised to visit the outpatient clinic or emergency department. The temperature will be measured on arrival at the outpatient clinic or emergency department, and the same additional examinations will be performed. A monitor will independently review the patient’s medical files in order to ensure that the pneumonia was actually present.

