## Methods/design

### Objective

The primary aim of this trial is to investigate the effect of ORIF versus nonoperative treatment on the occurrence of pneumonia within 30 days after trauma in adult patients who sustained multiple simple fractured ribs. The secondary aims are to investigate the effect of treatment on the need for and duration of mechanical ventilation, level of thoracic pain and analgesics use, (recovery of) pulmonary function, hospital and ICU length of stay, thoracic injury-related and surgery-related complications and mortality, secondary interventions, quality of life, and total costs (in-hospital and socio-economic) of treatment, health care consumption, and work absence. At the end, a cost-effectiveness analysis will be done.

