## Inclusion and exclusion criteria

The study population will consist of adults with three or more simple rib fractures after blunt force trauma. The fracture pattern will be diagnosed and delineated with a CT scan of the thorax, at least 64-slice and preferable including 3D reconstruction.

In order to be eligible to participate in this study, a patient must meet all of the following inclusion criteria:Age 18 years or olderFor any of the ribs number 4 to 10, three simple fracture ribs with either A) at least one fracture dislocated over one shaft-width; or B) unbearable pain (VAS or Numeric Rating Scale (NRS) >6 points)Blunt force traumaHospital presentation within 72 h after traumaProvision of informed consent by patient or proxy

A patient who meets any of the following criteria will be excluded from participation:Neurotraumatic changes leading to mechanical ventilation (GCS ≤ 8 at 48 h post-injury. If unable to assess full GCS due to intubation or other causes, GCS motor ≤ 4 at 48 h post-injury)Rib fractures due to cardiopulmonary resuscitationSurgical rib fixation not possible due to additional traumatic injuries (hemodynamically or pulmonary unstable, for example, based on parenchymal lung trauma) or the patient is unfit for surgery, to be decided by an ICU doctor, trauma surgeon, or anesthesiologistFlail chest, based on radiological or clinical findingsDecreased sensory or motor function due to (previous) cervical or thoracic spine failurePrevious rib fractures or pulmonary problems, requiring continuous oxygen use at home pre-traumaCongenital thoracic deformity (pectus excavatum, pectus carinatum, severe scoliosis, or kyphosis)Inhalation trauma or severe burns close to or inside the mouth or neckSurgical fixation of the ribs not feasible within 7 days after traumaPatient unwilling or unable to comply with the intervention or follow-up visit scheduleInsufficient comprehension of the Dutch language to understand the rehabilitation program and other treatment information in the judgement of the attending physicianParticipation in another surgical intervention or drug study that might influence any of the outcome parameters

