### Recruitment and randomization

Eligible persons presenting to the emergency department (ED) or referred from another hospital, with multiple, simple rib fractures will be informed about the trial at the ED or at the surgical ward after admission. After explanation of the study, eligible patients will receive written information and a consent form from the attending physician, the clinical investigator, or a research assistant. Patients meeting all eligibility criteria will be recruited within 1 day after hospital admission. As surgical rib fixation appears to be most beneficial when performed within 72 h after trauma, patients are stimulated to decide within this period. However, informed consent can be given by the patient as long as rib fixation can be carried out within 1 week after trauma. Should patients not be able to sign informed consent themselves, a legal representative will receive oral and written information about the study, in the hospital, by the attending physician, the clinical investigator, or a research assistant, and will be asked to consent with participation of the patient.

After signing informed consent by patient or proxy, participants are allocated to one of the two study arms (surgical stabilization or nonoperative treatment) using a web-based randomization program that will be available 24 h a day. Allocation will be at random and concealed, in a 1:1 ratio, and will be stratified by site. Variable block sizes will be used; in each block, both treatments will be represented equally. As the intervention cannot be blinded, it will in no case be necessary to break the randomization code.

As with many surgical trials, patients and surgeons cannot be blinded for the intervention. In order to reduce bias as much as possible, a research physician or research assistant will perform the follow-up measurements using a standardized protocol. Also, the treating surgeon or ICU doctor will identify the primary outcome (i.e., pneumonia) based on the definition as mentioned under outcome measures.

Participation is on a voluntary basis and participants are allowed to withdraw from the study at any time without specifying why. The general practitioner will be informed about the patients’ participation.

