## Operative allocation

Preoperative treatment is the same as in the nonoperative treatment group. ORIF should be preferably carried out within 72 h after trauma, but fixation within 1 week will not lead to exclusion. The surgical fixation will be conducted by a senior fracture management surgeon who has participated in at least five rib fracture fixation procedures. A surgeon in training with limited experience in rib fixation is allowed to work under supervision of an experienced surgeon.

Patients allocated to the surgical group will undergo ORIF using plates and/or splints. The decision on what rib fixation system to use is to the discretion of the treating surgeon, provided that the fixation system is CE-mark approved for rib fixation. Each system will be used according to the supplier’s protocol. The patient will receive an intravenous single prophylactic dose of a third-generation cephalosporin preoperatively. The incision will be planned, based preferably on a preoperative 3D reconstruction of the thoracic cage. The positioning of the patient and number of ribs fixated will be left to the preference of the operating surgeon. A minimally invasive technique will not lead to exclusion of the study. The ribs will be visualized using a muscle-sparing approach. After removing interpositioning tissue, fracture reduction will be carried out and the rib fixation device will be positioned and fixated. The use of interpleural space rinsing with warmed NaCl 0.9% or thoracoscopic visualization during rib fixation will be left to the judgement of the surgeon. If indicated, an interpleural drain is percutaneously placed in dorsocaudal direction, apart from the surgical wound. The wound is closed, using a wound drain if needed.

After surgery, the patient will be admitted to the ward or ICU depending on his/her clinical state. Participating hospitals are allowed to use their local protocol for interpleural and wound drainage. Postoperative physical therapy and supportive treatment may be prolonged if needed. Postoperative care and preoperative treatment are the same as for nonoperative management. Critical elements of the operative treatment will be recorded.

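### Primary outcome is counted from trauma, but randomisation comes later: pneumonia already present at allocation counts as an event and dilutes the treatment effect

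*Protocol article*

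**What the plan says.** The time origin is trauma throughout. The section on the primary outcome measure says "The primary outcome measure is pneumonia within 30 days after trauma", the Objective asks about the effect of treatment "on the occurrence of pneumonia within 30 days after trauma in adult patients who sustained multiple simple fractured ribs", and the abstract uses the same window.

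Allocation comes later. Under the inclusion criteria, patients may present up to 72 h after trauma. The section on recruitment and randomization says "Patients meeting all eligibility criteria will be recruited within 1 day after hospital admission", but also that "informed consent can be given by the patient as long as rib fixation can be carried out within 1 week after trauma". The order is explicit: "After signing informed consent by patient or proxy, participants are allocated to one of the two study arms". The section on operative allocation matches this, since "fixation within 1 week will not lead to exclusion".

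Nothing in the article separates early from later pneumonia:
- The nearest exclusion criterion concerns patients for whom fixation is not possible ("hemodynamically or pulmonary unstable, for example, based on parenchymal lung trauma") or who are judged unfit for surgery. It does not name pneumonia.
- The baseline and injury variables under Other data collected, and the covariates listed for the logistic model, do not include pneumonia status at randomisation.
- The review of events is described as follows: "A monitor will independently review the patient’s medical files in order to ensure that the pneumonia was actually present". It addresses presence, not timing.

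**The concern.** Every patient has a stretch of time that lies inside the outcome window but before allocation. Take a patient who meets the pneumonia definition on day 2 and is randomised on day 4. As written, this patient is a primary event in an intention-to-treat comparison of proportions, although neither treatment could have caused or prevented the pneumonia. The Objective asks what ORIF does to pneumonia, and events of this kind carry no information on that. They add the same expected amount to both arms, so the ratio of risks moves toward 1 and the variance rises. The cost-effectiveness ratio, expressed per pneumonia prevented, uses the same count.

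**Working it through.** **Inputs.** From Sample size calculation: 35% vs 15%, two-sided α 0.05, power 80%, 72 per group before allowance for loss. From the eligibility and recruitment sections: presentation up to 72 h, recruitment within 1 day of admission, consent possible until just under 1 week. If admission follows presentation at once, the intended latest recruitment is 3 + 1 = about 4 days after trauma. The share q with pneumonia at randomisation is **not given**. The values 1%, 3%, 5% and 10% are assumptions.

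**Formula.** Pooled normal approximation, with d = p1 − p2 and p̄ their mean:

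power = Φ{ [d√n − 1.96√(2p̄(1−p̄))] / √[p1(1−p1) + p2(1−p2)] }

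**The plan's own figure.** With d = 0.20, p̄ = 0.25 and n = 72: (1.697 − 1.200) / 0.596 = 0.834, so power is 79.8%. The same formula solved for 80% gives 73 per group, so the stated 72 is reproduced to within one patient.

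**Case A: 35% and 15% apply to patients free of pneumonia at randomisation.** As written, the observed risks are q + (1−q)×0.35 and q + (1−q)×0.15. At q = 5% they are 38.25% and 19.25%, and (1.612 − 1.255) / 0.626 = 0.572, so power is 71.6%.

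Two repairs can be compared:
- *Kept, not counted:* prevalent cases stay in the denominator as non-events. The risks are (1−q)×35% and (1−q)×15%. The difference is still (1−q)×20 points, exactly as when they are counted, and only the risk ratio and the variance improve.
- *Set aside:* the comparison is made in patients free of pneumonia at randomisation. The risks are 35% and 15% with 72×(1−q) per group. At q = 5%, n = 68.4 and (1.654 − 1.200) / 0.596 = 0.762, so power is 77.7%.

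| q | Risks as written | Difference (points) | Risk ratio | Power as written | Kept, not counted | Set aside |
|---|---|---|---|---|---|---|
| 0 | 35% vs 15% | 20.0 | 0.43 | 79.8% | 79.8% | 79.8% |
| 1% | 35.65% vs 15.85% | 19.8 | 0.44 | 78.1% | 79.2% | 79.4% |
| 3% | 36.95% vs 17.55% | 19.4 | 0.47 | 74.9% | 78.1% | 78.5% |
| 5% | 38.25% vs 19.25% | 19.0 | 0.50 | 71.6% | 77.0% | 77.7% |
| 10% | 41.5% vs 23.5% | 18.0 | 0.57 | 63.8% | 73.9% | 75.4% |

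**Case B: 35% and 15% already include early cases.** The observed rates are then the planned ones and power stays at 79.8% for any q. The risks among patients free of pneumonia at randomisation are (0.35−q)/(1−q) and (0.15−q)/(1−q). At q = 5% these are 31.6% and 10.5%, a risk ratio of 0.33. The trial would report 0.43. The estimate is diluted although the plan loses no power.

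**The case against.** **The size is unknown.** This stands. No figure for q appears in the article. One week is the ceiling for consent; the intended course is recruitment within 1 day of admission, with patients encouraged to decide within 72 h. The exclusion for instability or unfitness for surgery will remove some early cases. A reader might infer that a week of uncontrolled time is typical or that the loss of power is known to be large, and the documents support neither.

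**The planning rates may already contain early pneumonia.** This also stands. They come from a Cochrane review and a retrospective analysis that are not shown, and their time origin cannot be checked. In that case there is no shortfall against the plan. A harsher calculation is tempting: hold the control rate at 35% including early cases, and apply the ratio 15/35 only to the remainder. It gives 71%, 65% and 48% power at q = 3%, 5% and 10%. It takes the 35% as already including early cases but treats the ratio from the same sources as free of them, so it should not be relied on.

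**There is no bias toward an arm.** Correct. A reader might infer that early events favour one treatment, but they precede randomisation and balance in expectation, though not exactly in any one trial. The harm is attenuation and imprecision.

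**Dating onset adds an unblinded judgement.** The treating surgeon or ICU doctor identifies pneumonia and knows the allocation. The trauma-anchored count does not need that dating. This is a fair cost. It is limited if status is recorded before allocation is known and the monitor checks the date.

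**The article is condensed.** The full protocol may handle prevalent cases, and the pneumonia flow diagram is not shown. But the article itself states the time origin in three places and does not leave it open.

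**Conclusion.** The point holds. The outcome window opens at trauma, allocation follows by days, and nothing in the article keeps pneumonia that precedes allocation out of the primary count. The direction is certain: the risk ratio moves toward 1 and variance rises. The size is not. If the planning rates describe patients free of pneumonia at randomisation, power at 72 per group falls from 79.8% to between 78% (q = 1%) and 64% (q = 10%). If the rates already include early cases, planned power is unaffected and only the estimate is diluted. Both readings rest on an assumed q that is equal in the two arms in expectation. This does not invalidate the trial or tilt it toward either treatment. It is a weakness in the event definition that should be corrected because correction is cheap.

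**What to change.** 1. Define the primary event as pneumonia with onset after randomisation and up to day 30 after trauma. Onset between randomisation and surgery remains an event.
2. Record at randomisation, before the allocation is known, whether the CDC criteria are already met.
3. Make the primary comparison, as randomised, in patients free of pneumonia at that point. This is a pre-randomisation characteristic, so the randomised comparison is preserved. Simply not counting prevalent cases while keeping them in the denominator would leave the risk difference at (1−q)×20 points.
4. Report the trauma-anchored count in all randomised patients as a sensitivity analysis.
5. Have the monitor check the onset date as well as the presence of pneumonia.

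Under Case A this gives about 79.4%, 78.5%, 77.7% and 75.4% power for q of 1%, 3%, 5% and 10%.

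**Cost.** One baseline status field and an onset date. The date is obtainable from the daily admission assessments and medical files, but the article does not say that it is recorded. The primary analysis set is slightly smaller, and comparability with series counted from trauma is less direct, which the sensitivity analysis covers. Eligibility and treatment are unchanged.

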**Fig. 1 Fig1:**
[figure not shown]
Pneumonia flow diagram, as designed by the CDC [42]. For further details of the flow chart, see the website of the CDC [42]

#### Secondary outcome measures

The secondary outcome measures are:Need and duration of mechanical ventilation in days. The number of days of invasive mechanical ventilation (by endotracheal tube or tracheostomy) from intubation until successful weaning will be determined. The need for mechanical ventilation will be evaluated based on arterial blood gas analysis and clinical performance of the patient. The duration of mechanical ventilation will be calculated from the dates of intubation and extubation. Re-intubation within 30 days will be recorded as well.Level of thoracic pain (NRS) and analgesics use. Thoracic pain will be determined using an 11-point Numeric Rating Scale (NRS) in which 0 implicates no pain and 10 the worst possible pain. Five thoracic pain levels will be analyzed: pain in rest, at night, during daily activities (e.g., work or hobbies), during maximal inspiration, and during self-care. Analgesics use during admission will be extracted from the medical files. After discharge, analgesics use will be asked for during the follow-up visits. Daily narcotic requirement will be calculated using an equivalence scale for 30 mg/day oral morphine.(Recovery of) pulmonary function. The parameters tidal volume (TV), forced vital capacity (FVC), inspiratory capacity (IC_lung_), and forced expiratory volume at 1 second (FEV_1_) will be determined using spirometry. Spirometry will be done by a member of the research team. During the spirometry, the patient has to inhale actively and exhale with maximum force possible. The mean of three tests will be calculated.Hospital length of stay expressed in days. This will be calculated as the time between admission and discharge from the hospital. Re-admission within 30 days will be added. Re-admission for thoracic reasons after 30 days and up to 12 months will be counted separately.ICU length of stay expressed in days. This will be calculated similarly to the hospital length of stay.Thoracic injury-related complications and mortality. The occurrence of thoracic injury-related complications will be recorded from the medical charts during clinical admission and each follow-up visit. Complications will be categorized for level of severity and treatment necessity according to the Clavien-Dindo classification [43]. Complications will include empyema (as diagnosed on CT scan, in presence of fever or positive cultures in the drained fluid), (retained) hydrothorax (a heterogeneous fluid collection with Hounsfield unit readings of 35–70 and evidence of pleural thickening) [44], nonunion (diagnosed on CT scan or operatively, at least 6 months after trauma) [45], and other (all other complications as judged by the treating physician). If mortality is caused by the thoracic injury or complication of thoracic injury, it will be counted in rates of mortality. Death caused by other reasons will be noted but excluded in this calculation.Surgery-related complications. The ORIF group can also develop hardware-related complications or failure. Hardware-related complication is superficial and deep wound infection which is defined as redness, tenderness, and warmth surrounding and in direct contact with the postoperative wound. Superficial infection leads to oral or IV antibiotics, and deep infection leads to surgical activity such as stitch removal of exploration of the wound. Hardware failure is defined as loosening of the plate, secondary dislocation of fixation material, malposition of hardware, and broken plates or splints.Secondary interventions to resolve complications. Secondary interventions within 12 months after trauma to relieve pain, treat infection, or other rib fracture-related problems will include the following: antibiotic therapy (both oral and intravenous), additional surgical interventions (e.g., surgical stabilization of nonunion, evacuation of hematoma, evacuation of empyema, removal of failed hardware, symptomatic hardware removal, and treatment of infection), and additional percutaneous interventions (e.g., for persistent bleeding intercostal artery, intraparenchymal bleeding, drainage of infection, and drainage of pleural fluid).Health-related quality of life measured using the Short Form-12 (SF-12) and EuroQoL-5D (EQ-5D) questionnaires. The SF-12 analyzes global health status, functional scale, and symptom scale. The score will be calculated based on eight domains and summarized into a Physical Component Summary (PCS) and Mental Component Summary (MCS). Data will be reported as utility score, ranging from 0 to 1 with a higher value indicating better quality of life. As a reference, the US population of 1998 will be used [46]. The EQ-5D is the most commonly used quality of life instrument for (rib) fracture patients [47, 48]. The EQ-5D is recommended for assessment of quality of life in trauma patients, especially for economic evaluation [49, 50]. The EQ-5D-5 L descriptive system consists of five dimensions of health (mobility, self-care, usual activities, pain/discomfort, and anxiety/depression), each with five possible answers. The patients’ health states will be converted into a utility score using the Dutch tariff [51]. Utility scores range from 0 to 1 with lower scores indicating poorer quality of life.Cost-effectiveness and health care consumption. Economic evaluations will be done from a societal perspective. The validated Medical Consumption Questionnaire (iMCQ) and Production Consumption Questionnaire (iPCQ) will be used. iMCQ details medical specialist care, physical therapy, hospitalization, nursing home, home care, and other costs directly associated with diagnosis, treatment, and rehabilitation. iPCQ comprises work resumption and production losses. Health care costs and lost productivity until 1 year after trauma will be measured in accordance with economic guidelines [52].

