
### Other data collected

In addition to the outcome measures, the following data will be collected in order to assess similarity between the treatment groups:

Intrinsic variables (baseline characteristics): age, gender, body mass index (BMI), American Society of Anesthesiologists (ASA) grade, tobacco consumption, comorbidities, and medication use.

Injury-related variables: injury mechanism, pleura drain placed, number and location of rib fractures, affected side, presence of sternum fracture, additional injuries represented by the Abbreviated Injury Score (AIS) [53], and Injury Severity Score (ISS).

Intervention-related variables: surgical approach, number of plates and splints used and for which ribs, surgical delay, primary and secondary surgeon (resident or staff surgeon), wound drain, intra-operatively placed interpleural drain including duration of drainage, and duration of surgery.

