### Study procedures

Patients will be followed until 12 months after trauma. Clinical evaluation will occur daily during hospital admission. After discharge, outpatient clinic evaluation will occur at 2 weeks (window 7–21 days), 1 month (window 21–39 days), 3 months (window 11–15 weeks), 6 months (window 24–28 weeks), and 12 months (window 12–14 months). These visits are standard of care for the targeted patient group. A schedule of events is shown in Table 1. Baseline data and perioperative data will be collected from the patients’ medical files as soon as possible, but no later than the first outpatient department visit. At the 12-month follow-up contact, the surgeon or research assistant will document any secondary intervention that may be planned for the patient.

**Table 1 Tab1:** Schedule of events (duration after trauma)

Radiographs and event forms	Screening	Enrolment	Pre-surgery	Surgery	Post-surgery (until day 7*)	2 weeks (7–21 days)	30 days (21–39 days)	3 months (11–15 weeks)	6 months (24–28 weeks)	12 months^$^ (12–14 months)
CT-scan	X								X	
Screening	X									
Informed consent		X								
Randomization		X								
Baseline data			X	X						
Intervention/surgical report form				X	X					
Outpatient clinic FU						X	X	X	X	X
Spirometry							X	X	X	X
Analgesic use			Daily, afternoon		Daily, afternoon	X	X	X	X	X
Pain (NRS-rest and inspiration)			Daily, afternoon		Daily, afternoon	X**	X	X	X	X
Pain (NRS-night, daily, and care)						X**	X	X	X	X
QoL (EQ-5D and SF-12)						X**	X	X	X	X
Complications			X	X	X	X	X	X	X	X
(Secondary) interventions			X		X	X	X	X	X	X
iPCQ and iMCQ questionnaire						X***	X	X	X	X
Early withdrawal						****	****	****	****	****

*Post-surgery

^$^May be planned at the patients’ residency

**Asking for current and pre-trauma status

***Asking for pre-trauma situation

****Only if applicable.

After 6 months, a thoracic CT scan is repeated. Pulmonary function will be tested during the outpatient clinic visits at 1, 3, 6, and 12 months. At each follow-up visit, the coordinating researcher or research assistant will ascertain patient status (i.e., adverse events/complications or secondary interventions) and will verify information within the medical records. At each visit, patients will be asked to complete questionnaires relating to their pain (NRS), analgesics use, quality of life (QoL) (SF-12 and EQ-5D), and health care use (iPCQ and iMCQ).

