Multivariable analysis will be done as secondary analysis. A logistic regression model will be developed, with pneumonia as dependent variable and treatment as covariate. Nonoperative treatment will serve as reference category. Baseline and injury-related variables that may potentially confound the association between treatment and outcome will be included in this model as covariate. These will be selected from literature and from data of this study (see Other data collected). Known potential confounders according to literature data are the number of rib fractures and age. Other potential confounders collected as part of this study are gender, ASA, COPD, osteoporosis, and additional injuries (ISS ≥ 16 versus ISS < 16, and presence versus absence of severe injuries (AIS ≥ 3) for any body region). Variables that produce a *p* value < 0.2 in the univariate analysis will be included in the regression model. Odds ratios will be reported with their 95% confidence interval and *p* value.

Continuous outcomes repeatedly measured over time will be compared between treatment groups using linear mixed-effects regression models (with fixed effects for treatment and other covariates like gender and age, if applicable). The interaction between treatment and time will be included to test for differences between groups over time. For each follow-up moment, the estimated marginal mean will be computed per treatment group and compared post hoc with a Bonferroni test in order to correct for multiple testing.

Other continuous and binomial variables will be tested with multivariable linear and binary logistic regression models, respectively. The outcome measure will be entered as dependent variable and treatment as covariate. Nonoperative treatment will serve as the reference group. Baseline and injury-related variables that may potentially confound the association between treatment and outcome will be included in the models as covariate. Coefficients will be reported with their 95% confidence interval and *p* value.

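### Spirometry: recovery has no reference value and height is not a named covariate, so per-visit comparisons in litres would be unbiased but less precise than they need be

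*Protocol article*

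**What the plan says.** **Outcome.** Under Secondary outcome measures, the Protocol article labels the endpoint '(Recovery of) pulmonary function' and states: "The parameters tidal volume (TV), forced vital capacity (FVC), inspiratory capacity (IC_lung_), and forced expiratory volume at 1 second (FEV_1_) will be determined using spirometry". The only derivation rule is "The mean of three tests will be calculated". It mentions no percent predicted, z-score or change score.

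**Timing.** Study procedures states: "Pulmonary function will be tested during the outpatient clinic visits at 1, 3, 6, and 12 months". Table 1 agrees: there is no spirometry at screening, before surgery, in hospital or at 2 weeks.

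**Model.** Statistical analyses assigns repeated continuous outcomes to linear mixed-effects models "with fixed effects for treatment and other covariates like gender and age, if applicable". A treatment-by-time interaction is included, and estimated marginal means are compared between arms at each follow-up moment.

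**Inputs on file.** Other data collected lists age, gender and BMI among the baseline characteristics. Height is not listed separately.

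**Contrast with other outcomes.** For pain and quality of life, the Table 1 footnote at the 2-week visit reads "Asking for current and pre-trauma status". SF-12 has a named reference population and EQ-5D a named tariff. Spirometry, the outcome whose label contains the word recovery, has no such anchor.

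**The concern.** Recovery needs something to recover to. The schedule rules out a patient's own earlier value, and the text names no predicted value. What remains is a volume at each visit, and FVC and FEV1 vary strongly with height, age and sex. The trial enrols adults from 18 with no upper age limit, and the Background describes both younger high-energy and elderly low-energy injuries, so that variation will be wide.

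Two things are at stake. One is interpretation: a volume in litres does not show how far a patient has recovered. The other is precision: variance that known patient characteristics could explain stays in the error term of the per-visit comparisons. The Background says earlier spirometry studies comparing operative and nonoperative treatment contradict each other, so precision is what a new trial can add. Gender and age are only conditional, and height, which must be known to calculate BMI, is not named.

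**Working it through.** **1. The plan's own design figure.** The only sample-size figure is for pneumonia: 35% versus 15%, two-sided 0.05, power 0.80, 72 per group. The pooled two-proportion formula gives 73, so it reproduces to within one patient. No SD, effect size or power is given for spirometry, so everything below rests on assumptions. After the stated 25% loss, 90 per group leaves 90 × 0.75 = 67.5, taken as 68 per arm.

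**2. Assumed inputs (none in the documents).**
- Predicted FVC in litres, with H height in metres and A age in years: men 5.76H − 0.026A − 4.34; women 4.43H − 0.026A − 2.89.
- 70% men; age mean 58, SD 16.
- Natural scatter of about 11% around predicted.
- Mean injury deficit 15% of predicted, with between-patient SD of 10 to 20 points.
- Mean heights of 1.78 to 1.80 m (men) and 1.65 to 1.67 m (women), SD 7 and 6.5 cm. Heights in this range reproduce the SDs below to within about 0.02 L.

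**3. Residual SD of FVC at one visit** (400,000 simulated patients, least squares):

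| Covariates | Deficit SD 10 points | Deficit SD 20 points |
|---|---|---|
| none | 0.94 L | 1.18 L |
| age, sex | 0.65 L | 0.96 L |
| age, sex, height | 0.57 L | 0.91 L |

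**4. Sample-size equivalent** = (SD without covariate ÷ SD with covariate)².
- Age and sex versus age, sex and height: (0.65/0.57)² = 1.30; (0.96/0.91)² = 1.11. The standard error is √1.11 to √1.30, or 1.05 to 1.14 times as large.
- No covariates versus all three: (0.94/0.57)² = 2.7; (1.18/0.91)² = 1.7. Repeat runs with slightly different height assumptions reach 2.9 at the upper end.

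**5. Power at one visit** for 0.28 L (7% of a mean predicted FVC of about 4.0 L), 68 per arm: Φ(0.28 ÷ (SD × √(2/68)) − 1.96).
- No covariates: 28 to 41%.
- Age and sex: 40 to 71%.
- Age, sex and height: 43 to 82%.

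**6. Sensitivity.**
- With natural scatter set to zero, the gain from adding height to age and sex rises to about 1.6.
- Assuming R² directly (age and sex / plus height: 0.3/0.5, 0.4/0.6, 0.5/0.65, 0.5/0.7) gives standard-error ratios of 1.18, 1.22, 1.20 and 1.29. These pairs let height add 0.15 to 0.20 to R². In step 3 it adds less: (0.65² − 0.57²)/0.94² = 0.11 and (0.96² − 0.91²)/1.18² = 0.07. The figures in step 4 are therefore the more cautious ones.

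**7. Treatment-by-time contrast.** Height is constant within a patient and largely cancels from change between visits. Assuming a mean gain of 10 points (SD 8), a 4-point difference between arms and 68 per arm, power for within-patient change is 78% in litres and 83% in percent predicted. As a sample-size ratio this is (1.96 + 0.95)²/(1.96 + 0.77)² = 1.14.

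**The case against.** The strongest reply is that the article never says litres are analysed. Averaging three tests describes how repeat readings at one visit are combined; it does not exclude later conversion to percent predicted. The unit of analysis for one secondary outcome is the kind of detail that a condensed article leaves to the full protocol or analysis plan. This stands, and the point is therefore conditional on an analysis in litres.

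Recovery can also be read as the course from 1 to 12 months, which the treatment-by-time term addresses. This stands too, though the article does not say that this is the meaning. A pre-injury spirometry value is not obtainable in acute trauma, so its absence is not in itself a planning error.

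A reader might infer that body size distorts the comparison between arms, for instance because an impaired tall young man can outscore a recovered small older woman. The documents do not support that. Allocation is concealed, 1:1 and stratified by site, so height, age and sex are balanced in expectation, and the trial compares arm means rather than such pairs of patients.

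A reader might also take the no-covariate power figures as the plan's own. They apply only if the covariates that Statistical analyses names are dropped.

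What the reply does not remove is that the article does describe the model, leaves age and gender conditional, does not name height, and compares marginal means visit by visit.

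**Conclusion.** The point holds as a matter of precision and interpretation, not of bias. Recovery is tied to no reference, and the stated covariate rule does not secure an adjustment whose inputs should already be at hand. If volumes are analysed in litres, the per-visit comparisons lose the equivalent of about 1.1 to 1.3 times as many patients relative to a model with age and sex, and about 1.7 to 2.9 times if no covariates enter. The treatment-by-time contrast loses little.

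These ratios rest on assumed FVC equations, heights, natural scatter and spread of injury deficit. They shrink as the deficit varies more between patients and grow as natural scatter falls. The outcome is secondary and the pneumonia analysis is unaffected. The documents do not support the stronger statement that the plan commits to unreferenced raw values.

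**What to change.** **Statistical analyses.** For the mixed models of all four spirometry parameters (TV, FVC, IC and FEV1), replace the conditional wording with age, sex and height as fixed covariates.

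**Other data collected.** Record height as its own variable alongside BMI.

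**Secondary outcome measures.** State the unit of analysis. Then either present FVC and FEV1 also as percent predicted or z-score from one named reference equation, as the measure of recovery, or define recovery as the change from 1 to 12 months.

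**Cost.** A few sentences. No extra visit or test is needed, since height is required for BMI anyway. The one drawback is that percent predicted depends on the chosen equation; keeping the covariate-adjusted analysis in litres beside it limits that dependence.
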